#### Sample and procedure: B) Health record reviews

Health record reviews will be conducted for all children with a cancer diagnosis who received treatment at one of the 16 pediatric oncology programs and died in the 12 months prior to the pre-test data collection (January 2014 to January 2015) and in the 6 months prior to the post-test data collection (June to November 2016).

Eligible deceased children will be identified through the Health Records Department. An on-site RA will review the health record and enter data directly into REDCap™. Data collection forms were developed based on previous health record reviews for children with cancer [9, 31, 32] and include information on diagnosis, age, location of death, involvement of a palliative care team, time spent in hospital during the last month of life, use of cancer directed treatments, and documentation of discussion of goals of care.

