### Stream 3 - Quality of care

Data collection and analysis in Stream 3 will address the impact of EPEC®-Pediatrics on the quality of palliative care provided to children with cancer and their families. Quality of palliative care will be assessed using data from three sources: A) surveys about symptoms, quality of life, and care quality completed by children receiving active treatment and their parents; B) review of health records of deceased patients; and C) surveys with bereaved parents about the quality of their children’s end-of-life care. Baseline data will be collected through each of the 16 pediatric oncology programs from January to April 2015, to provide a cross-sectional view of the quality of palliative care prior to the EPEC®-Pediatrics roll-out. The same data will be collected again from September to November 2016 to determine the impact of the roll-out on care quality.

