#### Sample and procedure: C) Bereaved parent surveys

During the pre and post-test period, bereaved parents will be invited to complete a survey about the quality of their children’s end-of-life care. Potential participants will be identified according to the following inclusion criteria: 1) Child died following a cancer diagnosis; 2) Child aged 19 years or younger; 3) Parents are able to read English or French. Parents will be excluded if: they requested to have no further contact from the hospital such as for bereavement follow-up support. Bereaved parents will not be approached about the study until at least 6 months have passed since the time of the child’s death. Therefore, in order to achieve the required sample size we will invite parents whose child died during a 2 year window that ends 6 months prior to the end of the pre-test data collection period (e.g. Invitation letters would be sent in January 2015 to bereaved parents whose child died between July 2012 and July 2014) and in an 8 month window that ends 6 months prior to the end of the post-test data collection period (e.g. Invitation letters would be sent in January 2017 to bereaved parents whose child died between December 2015 and July 2016).

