#### Sample size

The majority of quality indicators are categorical in nature (i.e., proportion of children who die in preferred location, proportion of children/parent who report symptoms in the severe range); therefore, sample size for this component of the project was calculated based on categorical analytic techniques. Specifically, sample size for standard Chi-square analysis was conducted and increased by a factor equivalent to the assumed design effect due to the clustering within regions. Given the timeline for the project and the number of children that die from cancer across Canada in a given year (~200), we will only be able to collect data on 100 deceased children in the 6 months following project implementation. However, retrospective health record reviews and surveys can be completed for a larger number of children at baseline. A prior study examining the effect of unit level interventions across 16 pediatric units across Canada, demonstrated moderate intra-class correlations (ICCs) for knowledge outcomes, but negligible ICCs for process and clinical outcomes [35]; therefore, a small ICC of 0.01 was used to adjust the sample size estimate to account for clustering within sites. We will complete a minimum of 200 health record reviews/surveys at baseline and 100 in the post-implementation period across all 16 sites to detect a 15 % difference in outcomes with 80 % power.

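### The post-test death window overlaps its own collection period, leaving recent deaths 0 to 6 months to become known against about 3 to 16 months at baseline

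*Protocol article*

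**What the plan says.** Under Stream 3, part B (Health record reviews), the protocol article covers all children with cancer treated at one of the 16 programmes who died in a stated window. On case-finding it says: "Eligible deceased children will be identified through the Health Records Department". No other source is named.

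The dates are these:

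- Baseline deaths: "died in the 12 months prior to the pre-test data collection (January 2014 to January 2015").
- Baseline collection, from the Stream 3 introduction: "Baseline data will be collected through each of the 16 pediatric oncology programs from January to April 2015".
- Post-test deaths: "in the 6 months prior to the post-test data collection (June to November 2016").
- Post-test collection, from the Stream 3 introduction: "The same data will be collected again from September to November 2016".
- Part C (Bereaved parent surveys) carries a later date: "Invitation letters would be sent in January 2017 to bereaved parents whose child died between December 2015 and July 2016".

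The review forms "include information on diagnosis, age, location of death, involvement of a palliative care team", among other items. The Sample size section gives as an example of a quality indicator the "proportion of children who die in preferred location". It sets a minimum of 200 reviews or surveys at baseline and 100 after implementation, to detect a 15 % difference.

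**The concern.** A pre-post comparison of deceased children needs the two death lists to be about equally complete. At baseline the death window closes as collection opens, so the list can settle for some three months before collection ends. At post-test the death window contains all three collection months, although part B describes it as preceding collection. When post-test collection opens on 1 September 2016, half of the window has not yet happened, and the last eligible deaths have no time to be recorded before collection closes.

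This matters if the time for a death to become known depends on where the child died. A treating hospital would be expected to record its own deaths directly, whereas a death at home, in a hospice or in another hospital has to be reported to it. Entry into the sample would then depend on place of death, and more strongly at post-test. The planned GEE model on time point allows for clustering within regions, but it cannot restore children who never reached the list.

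**Working it through.** **The plan's own count.** The Sample size section expects about 200 cancer deaths a year, so six months give 200 × 6/12 = 100. The required post-test minimum is also 100, so there is no margin for missed deaths.

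**Time from death to the end of collection.**

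| Period | Earliest death | Latest death | Collection ends | Longest | Shortest | Mean |
|---|---|---|---|---|---|---|
| Baseline | 1 Jan 2014 | 1 to 31 Jan 2015 | 30 Apr 2015 | 15.9 months | 2.9 to 3.9 | 9.4 to 9.9 |
| Post-test, Stream 3 dates | 1 Jun 2016 | 30 Nov 2016 | 30 Nov 2016 | 6.0 | 0 | 3.0 |
| Post-test, if January 2017 applies | 1 Jun 2016 | 30 Nov 2016 | 31 Jan 2017 | 8.0 | 2.0 | 5.0 |

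The mean time available differs about threefold on the Stream 3 dates (9.4 / 3.0 = 3.1) and about twofold on the January 2017 date (9.4 / 5.0 = 1.9).

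**What this could do to location of death.** The documents give no registration delay, so every value in this part is an assumption. Suppose that hospital deaths are known at once, that deaths elsewhere are registered after an exponential delay with mean L months, that deaths are spread evenly over the window, that the list is read at the end of collection, and that the true out-of-hospital share h does not change.

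If the available time runs from a to b months, the captured share of out-of-hospital deaths is

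c = 1 − L(e^(−a/L) − e^(−b/L)) / (b − a),

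and the observed out-of-hospital share is h·c / (h·c + 1 − h).

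Example with h = 0.40 and L = 2:

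- Baseline (3 to 15.9 months): c = 0.965, observed 0.386 / 0.986 = 39.2 %.
- Post-test (0 to 6 months): c = 0.683, observed 0.273 / 0.873 = 31.3 %.
- Spurious change: −7.9 points. Of 100 post-test deaths, 60 + 40 × 0.683 = 87 are found.

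| Assumed mean delay L (months) | Captured, baseline | Captured, post-test | Change at h = 40 % | Change for h = 30 to 60 % | Found of 100 at post-test (h = 40 %) |
|---|---|---|---|---|---|
| 0 | 1.000 | 1.000 | 0 | 0 | 100 |
| 0.5 | 1.000 | 0.917 | −2.1 points | −1.8 to −2.2 | 97 |
| 1 | 0.996 | 0.834 | −4.2 | −3.6 to −4.4 | 93 |
| 2 | 0.965 | 0.683 | −7.9 | −6.6 to −8.5 | 87 |
| 3 | 0.916 | 0.568 | −10.4 | −8.6 to −11.9 | 83 |

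**If the January 2017 date applies** (2 to 8 months; h = 0.40, L = 2): c = 1 − 2(e^(−1) − e^(−4))/6 = 0.883, observed 0.353 / 0.953 = 37.1 %, change −2.1 points.

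**With the list closed 3 months after the last death** (3 to 9 months; same h and L): c = 1 − 2(e^(−1.5) − e^(−4.5))/6 = 0.929, observed 0.372 / 0.972 = 38.3 %, change −0.9 points.

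**The case against.** The strongest reply is that the mechanism is not in the document. Nothing in the article describes how or when Health Records learns of a death outside hospital, how long that takes, or how complete the list is. With no delay there is no bias, and the table above is arithmetic on assumed values. This stands, and it limits the point to a conditional one.

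A reader might infer that Health Records is the sole source. The article names no other, but it does not exclude cross-checks, and a condensed article may leave site-level case-finding to the full protocol. In part C, clinicians who cared for the family or provide bereavement follow-up send the letters, so people who know of deaths take part in the study. The text does not say that they feed the review list.

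The zero lag also depends on which date governs. Part B's own wording would put review after the window, and part C's rule, which closes its window six months before the end of post-test collection, points to January 2017. That reading shortens the gap without closing it. It is also uncertain: the same rule applied to part C's baseline example gives January 2015, whereas Stream 3 ends baseline collection in April 2015.

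Finally, the date on which the list is drawn is not given for either period. A baseline list drawn in January 2015 and never refreshed would also have little lag for its latest deaths. This is a reason to state the date in both periods.

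**Conclusion.** The point holds in a limited form. The stated dates give post-test deaths much less time to become known than baseline deaths: 0 to 6 months, or about 2 to 8 on the January 2017 reading, against about 3 to 16. The post-test window also contradicts its description as preceding collection.

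If out-of-hospital deaths reach Health Records later than in-hospital deaths, the observed out-of-hospital share would fall spuriously and the post-test count would drop below 100. The size is unknown. It is zero without delay and, under the model above, roughly 2 to 9 points for mean delays of half a month to two months, against a 15-point target.

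A reader might go further and conclude that location of death is biased, or that the error works against the roll-out. The documents support neither. No delay is described, and the named indicator is death in the preferred location. The article does not say that death outside hospital is the desired result, nor how preference relates to place.

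**What to change.** 1. Reconcile the post-test dates in the Stream 3 introduction, part B and part C, and state when the death list is drawn in each period.
2. Draw or re-run the post-test list at a fixed lag of about 3 months after the last eligible date of death. With a window ending 30 November 2016 this means the end of February 2017. It matches the baseline minimum, from the end of January to the end of April 2015.
3. Alternatively, end the post-test death window about 3 months before collection closes. March to August 2016 with review to the end of November would give the same 3 to 9 months.
4. Where a site already holds an oncology or palliative-team list, a cross-check is a useful option. Baseline case-finding need not be redone.

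The cost of item 2 is that review of the last post-test records ends about 3 months later. Part C already plans study activity in January 2017, so the extension beyond that is about one month. Item 3 keeps the calendar but takes in deaths from earlier in the roll-out, although the Sample size section describes the post-test deaths as those in the six months after implementation. Item 2 is therefore preferable. Neither makes the lags identical, since baseline deaths still have a longer maximum, but in the worked example the spurious change shrinks from −7.9 to −0.9 points.

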#### Sample and procedure: C) Bereaved parent surveys

During the pre and post-test period, bereaved parents will be invited to complete a survey about the quality of their children’s end-of-life care. Potential participants will be identified according to the following inclusion criteria: 1) Child died following a cancer diagnosis; 2) Child aged 19 years or younger; 3) Parents are able to read English or French. Parents will be excluded if: they requested to have no further contact from the hospital such as for bereavement follow-up support. Bereaved parents will not be approached about the study until at least 6 months have passed since the time of the child’s death. Therefore, in order to achieve the required sample size we will invite parents whose child died during a 2 year window that ends 6 months prior to the end of the pre-test data collection period (e.g. Invitation letters would be sent in January 2015 to bereaved parents whose child died between July 2012 and July 2014) and in an 8 month window that ends 6 months prior to the end of the post-test data collection period (e.g. Invitation letters would be sent in January 2017 to bereaved parents whose child died between December 2015 and July 2016).

The Bereaved Parent Survey was adapted from the SCCC [9, 31, 32] and QCECI [33] to mirror the survey used during active treatment, with additional items specific to the quality of end-of-life and bereavement care. Contact information (name and mailing address) of eligible parents will be obtained through Health Records. A letter about the study will be sent to eligible parents from someone who provided care to the family prior to the child’s death or who is providing bereavement follow-up. The letter will include a description of the study with instructions to access the survey online for submission via REDCap™. The letter will also provide contact information for a RA at the central study site if the parent wishes to complete the survey with the RA by telephone or to request a hard copy to complete and return by mail. When the parent accesses the survey online, the consent form will appear prior to commencing the survey questions along with a list of sources of support and information. Submission of the survey will signify consent. The invitation letter will also include a self-addressed stamped envelope to be returned to the originating site if the parent does not wish to have any further contact about the study (opt-out). If an opt-out letter has not been received, a thank you/reminder letter will be sent to all eligible parents 3-4 weeks after the initial contact.

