#### Data analysis

Categorical data (e.g., location of care/death) and continuous data (e.g., parent reports of care quality scores) and will be summarized and descriptively reported using frequencies and proportions or means and standard deviations, respectively. To identify differences in the quality indicators between baseline and following implementation, marginal regression models (i.e. Generalized Estimating Equation models) will be used to model the outcome on time point (i.e. pre- versus post-test) and account for clustering of outcomes and practices of care within regions. All analyses will be conducted using SAS v9.3. A *p*-value of 0.05 or less will be used to indicate statistical significance.

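### Bereaved parents are surveyed 6-30 months after the death at baseline but only 6-13 months after it post-test, and the stated pre/post model does not separate this lag from period

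*Protocol article*

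**What the plan says.** The Protocol article's section on bereaved parent surveys sets one minimum wait for both periods: "Bereaved parents will not be approached about the study until at least 6 months have passed since the time of the child’s death". It then sets windows of different length for the date of death. Baseline uses "a 2 year window that ends 6 months prior to the end of the pre-test data collection period", with the example "Invitation letters would be sent in January 2015 to bereaved parents whose child died between July 2012 and July 2014". Post-test parents are those whose child died "in an 8 month window that ends 6 months prior to the end of the post-test data collection period", with the example "Invitation letters would be sent in January 2017 to bereaved parents whose child died between December 2015 and July 2016". The reason given for the long baseline window is numbers: "in order to achieve the required sample size we will invite parents whose child died during a 2 year window".

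The Stream 3 Data analysis section says of the GEE models that they "will be used to model the outcome on time point (i.e. pre- versus post-test) and account for clustering of outcomes". It names no term for time since death. The Discussion raises intervention length, follow-up length and variation in roll-out between sites as limitations, but not the difference in lag.

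**The concern.** Parents in this survey look back on end-of-life care and report on bereavement care. If answers depend on how long ago the child died, through recall, stage of grief or time available for follow-up contact, two groups with different lags will differ even if care has not changed. Here the lag differs by period by design, and there is no concurrent control group. A contrast of pre- with post-test then mixes any effect of EPEC-Pediatrics with any effect of lag. More respondents would narrow the interval around that mixture without separating its parts.

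The bereaved-parent survey is one of three sources for the quality-of-care question, and bereavement support is the subject of one of the TIPS Kits, so the source bears on something the project sets out to change.

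**Working it through.** **Inputs.** From the bereaved parent surveys section: the 6-month minimum lag, the 24- and 8-month windows, and the example dates. From the Sample size section: 200 baseline and 100 post-test, a 15% difference, ICC 0.01, 16 sites. From Data analysis: significance level 0.05, taken here as two-sided.

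**1. Lag at invitation (letter month minus month of death).**

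| | Earliest death | Latest death | Lag range |
|---|---|---|---|
| Baseline, letters January 2015 | July 2012: 30 months | July 2014: 6 months | 6-30 |
| Post-test, letters January 2017 | December 2015: 13 months | July 2016: 6 months | 6-13 |

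By exact days, a death on 1 December 2015 with a letter on 31 January 2017 gives 14 months. The stated rule leads to the same place: with lag measured at the end of collection, windows of 24 and 8 months ending 6 months earlier give 6-30 and 6-14. The imbalance does not depend on the examples.

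**2. Mean lag, assuming deaths and responses spread evenly.**

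- Baseline: (6 + 30)/2 = 18 months.
- Post-test: (6 + 13)/2 = 9.5, or (6 + 14)/2 = 10 months.
- Gap: 8.5 or 8 months.

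**3. Baseline parents with no post-test counterpart.**

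- Post-test maximum 13: (30 - 13)/24 = 17/24 = 71%, leaving 200 × 7/24 = 58 comparable parents.
- Post-test maximum 14: (30 - 14)/24 = 16/24 = 67%, leaving 200 × 8/24 = 67.

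**4. What a lag effect would do (illustration only).** The documents give no rate at which answers change with time since death. Assuming a linear change, the spurious pre/post difference is the rate times the gap. At 0, 0.25, 0.5 and 1 percentage point per month over 8.5 months it is 0, 2.1, 4.3 and 8.5 points, against the 15-point target. Either sign is possible.

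**5. Power of a lag-matched comparison.** The design effect is 1 + (m - 1) × 0.01, with m respondents per site.

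- Baseline 58: m = 3.6, design effect 1.026, effective n = 56.5.
- Baseline 67: m = 4.2, design effect 1.032, effective n = 64.9.
- Post-test 100: m = 6.25, design effect 1.0525, effective n = 95.0.

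Power = Φ[(0.15 - 1.96 × SE0)/SE1], with SE0 from the pooled proportion and SE1 from the separate proportions. For 42.5% against 57.5% with 58 at baseline, SE0 = 0.0839 and SE1 = 0.0830, so power = Φ(-0.17) = 43%. The base rate is not stated, so a range is shown:

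| Proportions | Baseline 58 | Baseline 67 |
|---|---|---|
| 10% vs 25% | 63% | 68% |
| 20% vs 35% | 50% | 54% |
| 30% vs 45% | 45% | 48% |
| 42.5% vs 57.5% | 43% | 46% |
| 50% vs 65% | 44% | 47% |

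Fewer responders than 200 and 100 would lower these figures.

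**6. Dates to reconcile.** The Stream 3 introduction puts collection at January to April 2015 and September to November 2016. The January 2017 letters fall outside the second period. A window ending 6 months before the end of April 2015 would close about October 2014, not July 2014. Neither discrepancy removes the unequal window lengths.

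**The case against.** Four points can fairly be made for the plan.

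*The analysis may already adjust.* The article does not say that time point is the only term, and covariates and sensitivity analyses are commonly left to an analysis plan that is not shown here. This stands so far as it goes: a reader might infer a proven analysis error, and the text does not support that. What remains is that the article itself fixes both the unequal windows and the contrast, and nothing in it acknowledges that the two interact.

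*The windows are a reasoned trade-off.* With about 200 deaths a year and a 6-month wait, the post-test window could not reach back two years without taking in deaths from before the roll-out. This stands, and is a reason to keep the windows and deal with lag in the analysis.

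*No bias is shown.* This stands too. A reader might take the illustration in step 4 as an estimate, for instance that lag could account for half or more of the 15-point target. The documents supply no rate, and zero is possible. A reader might also infer that bereavement-care items are mechanically biased against the intervention because post-test parents have had less time to receive follow-up. The article says only that such items were added; wording and reference periods are not shown, so this cannot be concluded.

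*A covariate is not a clean cure.* With one letter date per period, months since death is calendar date of death under another name. At baseline it carries any secular trend; post-test, a shorter lag means a later death and longer exposure to the roll-out. This stands, and is why adjustment alone is not enough.

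**Conclusion.** The point holds as a design imbalance that the stated analysis does not address, and it should be fixed. The lag ranges follow exactly from the article's own dates. The means and the 67-71% assume deaths and responses spread evenly over each window. The confounding is partial, because lags overlap from 6 to 13 months, and it is confined to one of three quality-of-care sources. A reader might go further and hold that the bereaved-parent comparison is invalid, or that its bias has a known direction; the documents support neither. They support only this: a pre/post difference in these indicators, taken from the stated model alone, could not be read as an effect of the roll-out distinct from a difference in time since bereavement.

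**What to change.** Keep both windows. Derive months since death at invitation from the date of death, which sites already need to establish eligibility. For all bereaved-parent indicators, pre-state two analyses:

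1. A matched comparison of baseline deaths from December 2013 to July 2014 with the post-test cohort. At a January 2015 letter these have lags of 6-13 months, and the months of the year match as well.
2. A full-sample GEE that adds months since death to time point, with its functional form stated in advance.

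Report both beside the unadjusted result, and treat a pre/post change as supported only if the estimates agree in direction and rough size. Judge agreement on estimates and intervals, not on whether each reaches significance. Name the lag imbalance as a limitation, and reconcile the letter dates and windows with the stated collection periods.

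The cost is a derived variable and two pre-stated analyses. Two downsides need stating. The matched baseline subset is small, with the power shown above, so it supports the full-sample result and does not replace it. The adjusted estimate keeps all 200 baseline responses but relies on model form, because about two thirds of them lie at lags with no post-test data and because lag and date of death cannot be told apart within a period.

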In our study, the content of EPEC®-Pediatrics will not be changed; however, four key features will be added to the delivery process based on implementation science [27] to promote sustained improvement in the quality of palliative care for children with cancer and their families. 1) Rather than attending as individuals, Regional Teams of three to five health professionals representing oncology, palliative care, and the community (e.g., home care nurses, community pediatricians) will attend a Train-the-Trainer Conference together in 2015 and work as a team. 2) A second day will be added to the Conference to allow Regional Teams to review data collected in the pre-test period and use those data to develop regional dissemination strategies and plan their QI project. 3) The Research Team developed two additional TIPS Kits to provide a wider choice of QI projects. 4) Ongoing support will be provided by the Research Team for education and QI initiatives throughout the intervention period, 2015 - 2016. Teams will also communicate with each other via a listserv and webinars to share successes and challenges.

The effectiveness of our EPEC®-Pediatrics roll-out will be assessed according to four outcomes. The guiding research questions are: What is the impact of EPEC®-Pediatrics on: 1) the self-assessed knowledge of health professionals who take part in the curriculum; 2) knowledge transfer and dissemination outcomes; 3) practice change outcomes, and 4) the quality of palliative care provided to children with cancer and their families?

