## Methods/design

### Design

In this study we will use a pre-post-test design and an integrated knowledge translation (KT) approach with involvement of knowledge users and key-stakeholders through the project [28]. The pre-test period will begin in January 2015 and the post-test period will begin in the fall of 2016. This timeline allows for the educational rollout of EPEC®-Pediatrics and QI to occur over approximately 15 months. Data collection and analysis will occur in three streams in order to answer the research questions: 1) knowledge dissemination, 2) quality improvement, and 3) care quality. The study has been approved by the Research Ethics Board (REB) at the Hospital for Sick Children (#1000047116) as the primary site as well as by the relevant REB for each participating site (See Additional file 1 for a list of sites with the corresponding REB).

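### On the implied timeline, the bereaved-parent post-test deaths fall during the roll-out, and the post-test dates conflict, so this end-of-life comparison is before versus during the programme

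*Protocol article*

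**What the plan says.** The Design section gives the overall timeline: "The pre-test period will begin in January 2015 and the post-test period will begin in the fall of 2016". It adds: "This timeline allows for the educational rollout of EPEC®-Pediatrics and QI to occur over approximately 15 months". The Background section describes support "throughout the intervention period, 2015 - 2016". The section Stream 3 - Quality of care places baseline collection in January to April 2015, ahead of the roll-out, and says of the post-test: "The same data will be collected again from September to November 2016".

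For bereaved parents (Sample and procedure: C), the written rule is an eight-month window of deaths ending six months before post-test collection ends. No parent is approached until six months after the death. The example dates are: "Invitation letters would be sent in January 2017 to bereaved parents whose child died between December 2015 and July 2016".

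For health records (Sample and procedure: B), the post-test deaths are those "in the 6 months prior to the post-test data collection (June to November 2016".

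The Sample size section plans at least 200 reviews or surveys at baseline and 100 in the period it calls post-implementation, to detect a 15 % difference with 80 % power and an ICC of 0.01. The Stream 3 Data analysis section fits a GEE with time point coded as pre-test or post-test.

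**The concern.** A pre/post comparison measures a completed programme only if the post-test observations arise after, or near the end of, its delivery. For end-of-life care, exposure is fixed at the child's death and not when the parent fills in the survey. A survey sent in January 2017 about a death in December 2015 describes care given part-way through the roll-out.

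If such deaths are coded simply as post-test, and if the effect grows as teaching and QI are delivered, the estimate is pulled toward zero. A null result could not then separate a programme that does not work from one not yet fully delivered.

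Separately, the collection period and the death windows do not agree, so the text does not fix which bereaved parents belong to the post-test sample.

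**Working it through.** **Step 1: implied roll-out dates.** These are derived, not printed. Baseline ends in April 2015 and precedes the roll-out, so the earliest start is about May 2015. Adding 15 months gives an end in July 2016 (May start), August 2016 (June start) or September 2016 (July start).

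**Step 2: where the bereaved post-test deaths fall.** December 2015 to July 2016 is eight months, which matches the stated length. For each of the three starts, 8 of 8 months lie inside the roll-out. Sensitivity: an April start gives 7 of 8. A 12-month roll-out from May, June or July gives 5, 6 or 7 of 8.

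**Step 3: the written rule in place of the example.** Collection ends in November 2016, and six months earlier is May 2016. Eight months ending then is October 2015 to May 2016, which is earlier still.

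**Step 4: date conflicts.**
- A window ending in July 2016 fits the rule only if collection ends in January 2017, not November 2016.
- Under the six-month wait, parents of children who died in June or July 2016 can first be approached in December 2016 or January 2017, after the stated collection period.
- Collection starts in September 2016, so the six months before it are March to August. The printed record-review months, June to November, share three of those six and overlap collection by three months.

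**Step 5: illustration of size.** Assumptions: the effect builds linearly over 15 months; the test is two-sided at 0.05; the base rate is 50 % or 70 % (the protocol gives none). The midpoint of the death window is 1 April 2016, so mean exposure = (months from start to that date)/15.

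Design effect = 1 + (300/16 − 1) × 0.01 = 1.1775. Effective sizes are 200/1.1775 = 169.9 and 100/1.1775 = 84.9.

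Power = Φ[(d − 1.96·SE₀)/SE₁], with SE₀ pooled and SE₁ unpooled.
- 50 % vs 65 %: SE₀ = 0.0661, SE₁ = 0.0644; (0.15 − 0.1296)/0.0644 = 0.32; power 0.62.
- 50 % vs 59 %: SE₀ = 0.0663, SE₁ = 0.0657; (0.09 − 0.1300)/0.0657 = −0.61; power 0.27.

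| Start | Mean exposure | 15 points appears as | Power, 50 % base | Power, 70 % base |
|---|---|---|---|---|
| Undiluted | 1 | 15 | 0.62 | 0.76 |
| May 2015 | 11/15 = 0.73 | 11 | 0.38 | 0.47 |
| June 2015 | 10/15 = 0.67 | 10 | 0.32 | 0.39 |
| July 2015 | 9/15 = 0.60 | 9 | 0.27 | 0.32 |

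The protocol's 80 % can be neither confirmed nor refuted without a base rate. For example, 70 % vs 85 % with a design effect based on 100/16 per site, 1 + (100/16 − 1) × 0.01 = 1.0525, needs 196/98, close to the stated 200/100. The point here is the fall in power, not the starting value.

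**Step 6: record reviews, same assumptions.** The monthly exposure fraction for June to November 2016 is taken at mid-month and capped at 1.
- May start: (0.90 + 0.97 + 4 × 1)/6 = 0.98.
- June start: (0.83 + 0.90 + 0.97 + 3 × 1)/6 = 0.95.
- July start: (0.77 + 0.83 + 0.90 + 0.97 + 2 × 1)/6 = 0.91.

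Dilution there is small, at 2 to 9 %.

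**The case against.** The strongest reply is that no roll-out dates are printed, the bereaved windows are only examples, and the Discussion already concedes that a longer intervention and follow-up might show more. The Discussion also plans to relate differences in local roll-out (sessions, End-Users, QI projects) to quality of care across sites.

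Much of this is fair. The statement that all deaths fall inside the roll-out is an inference, and the size rests on assumed linearity. But treating the dates as examples does not help, because the written rule gives an earlier window. The Discussion's caveat does not say that the bereaved post-test deaths precede completion. The planned exploration is by site, not by exposure at the time of death.

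A reader might go further on several points that the document does not support:
- *That the whole Stream 3 comparison misses the completed programme.* The active-treatment surveys (September to November 2016) follow the implied roll-out, overlapping at most its last month under a July start. The record-review window straddles its end. Bereavement-care items can cover time after it.
- *That sites would review different health records.* The months June to November are printed, so the wording 'prior to' is probably a slip for prior to the end of collection.
- *That the baseline example is a material error.* Six months before the end of April 2015 is October 2014, not July 2014, but both precede the roll-out.
- *That the Sample size section sets a rival selection rule.* Its phrase, "we will only be able to collect data on 100 deceased children in the 6 months following project implementation", is a feasibility count. The wording should be aligned, but it selects no one.

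**Conclusion.** The point holds for the bereaved-parent end-of-life outcomes. On the protocol's own timeline, the post-test deaths occur while the roll-out is under way: all eight months for a May to July 2015 start, seven of eight for an April start. Calling them post-implementation is therefore not supported. That the shortfall in exposure pulls the estimate toward zero needs only that the effect grows with delivery. The size (15 points appearing as 9 to 11, and power falling to 0.27-0.38 at a 50 % base rate or 0.32-0.47 at 70 %) depends on linear build-up, a May to July start and the assumed base rates, and is an illustration.

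The conflict over dates needs no assumption. Collection in September to November 2016, a six-month wait and deaths up to July 2016 cannot all hold, and June to November is not the six months before a September start.

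**What to change.** 1. State the roll-out start and end dates. Reconcile the collection period and death windows in Stream 3 - Quality of care and in Sample and procedure B and C so that rule and dates agree, and align the Sample size wording.
2. Describe the bereaved-parent end-of-life comparison as before versus during roll-out. Do not conclude from a null result that the completed programme has no impact. Bereavement-care items can be described separately.
3. Keep the pre/post GEE. For deceased children, add a sensitivity analysis using the cumulative sessions or attendees at the child's site up to the date of death, taken from the quarterly Education Roll-out Reports. This extends the site-level exploration already planned in the Discussion.

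The cost is protocol wording, one derived variable and a more modest conclusion for one data source. The exposure variable is approximate because reports are quarterly. It is also not randomised, because sites choose what they deliver, and session counts do not capture the QI projects. It should therefore supplement the pre/post term and not replace it. Moving the bereaved deaths to after the roll-out is not proposed: with eight months of deaths and a six-month wait, a roll-out ending about August 2016 would put the last letters in late 2017.
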